To assess the safety and reactogenicity of MVA-NP+M1 in combination with licensed inactivated influenza vaccine in adults ≥65 years. To assess the immunogenicity of MVA-NP+M1 or Placebo in combination with the recommended licensed inactivated influenza vaccine in adults aged 65 years and above To assess the presence of the influenza virus using virological markers, in adults aged 65 years and above vaccinated with MVA- NP+M1 or Placebo in combination with the recommended annual licensed inactivated vaccine	6. Occurrence of solicited local and systemic reactogenicity signs and symptoms for 7 days following vaccination 7. Occurrence of unsolicited adverse events for 28 days following vaccination 8. Occurrence of serious adverse events throughout participants’ participation in the trial - Frequency of influenza-specific T-cells measured by IFN-γ ELISpot - Geometric mean titre of influenza-specific neutralising antibodies - Breadth of influenza-specific T-cells and antibodies 1. Incidence rate of laboratory confirmed influenza using RT-PCR.	Day 0–7 - Self-reported symptoms recorded using electronic or paper diaries Day 0–28 - Self-reported symptoms recorded using electronic or paper diaries Telephone calls on Day 1–3, day 7–9 and every 3–4 weeks throughout participants’ participation in the trial Blood samples drawn at enrolment (before vaccinations), day 21 and at the end of the influenza season Nasal swab sample taken by participant at the time of self-reported symptoms. Nasal swabs will be taken during the first 3 days of the onset of the self-reported symptoms
**Tertiary Objectives** To explore novel clinical endpoints for future Phase III efficacy trials of influenza vaccines	1. Estimated frequency of influenza infection using historical data on the proportion of ILIs that is caused by influenza virus infection.	At the end of the influenza season

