### Interventions

Participants are randomly assigned to either the control (licensed IIV and placebo) or intervention group (licensed IIV and MVA-NP+M1) by the Research Nurse.

***MVA-NP+M1*.** The vaccine has been described previously and consists of a replication deficient MVA viral vector expressing the NP and M1 antigens from the influenza A virus (H3N2, 87 A/Panama/2007/99) as a single fusion protein
^8^. A dose of 1.5 ×10
^8^ pfu will be used. MVA-NP+M1 is manufactured under good manufacturing practice conditions by Emergent Biosolutions, USA, and is certified and labelled for trial at the Clinical Biomanufacturing Facility, University of Oxford. The vaccine is stored at -80°C in a temperature monitored, secure freezer at the clinical sites.

***Seasonal influenza vaccine (licensed IIV)*.** Pre-packaged needle and syringe containing 0.5 ml licensed IIV (Split Virion) is stored at 2°C to 8°C in a secure, temperature-monitored refrigerator at site. 

***Placebo*.** Participants allocated to the control group will receive an intramuscular injection of 0.9% saline. The volume and site of injection will be the same as for the MVA-NP+M1 group.

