### Sub-cohort

A sub-cohort of participants (50 for each of two seasons) will be recruited to assess the immunogenicity of MVA-NP+M1 in combination with the licensed IIV. In addition to the procedures described for the main cohort, the sub-cohort attend a screening visit, and three further visits where blood samples are taken for monitoring of laboratory AEs and immunology purposes at weeks 1, 3 and 26. Blood samples will be stored in compliance with the Human Tissue Act (2004).

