***Immunogenicity analyses*.** In the immunology sub-cohort, the primary analysis will be to assess the difference in magnitude of influenza-specific T-cell (using interferon gamma enzyme-linked immunospot assay) and antibody responses (using influenza hemagglutination inhibition assay) between the two groups. We will assess the vaccine immunogenicity by comparing the change in these immunological parameters from baseline to 21 days after vaccination between the groups, and how this varies according to baseline factors of age, gender and chronic illness. To assess the durability of immune responses post-vaccination, the stability of immunological parameters between the post vaccine time point and end of season time point will be assessed. The immunological x will be log transformed (based 10) and we will use appropriate regression or correlation methods to carry out the analysis.

***Reporting procedures for adverse events*.** All adverse events (AEs) occurring in the first 28 days post-vaccination are captured in the diaries. The relationship of each AE to the trial medication is determined by a medically qualified individual. All AEs that result in a patient’s withdrawal from the study will be followed up until a satisfactory resolution occurs, or a non-study related causality is assigned. All reported severe symptoms are reviewed by the Medical Monitor in the first 4 weeks.

***Reporting procedures for SAEs*.** All SAEs are documented and reported according to the Pharmacovigilance SOP. The assessment of expectedness is made by a clinician using the reference safety information current at the time of the event. If deemed necessary un-blinding will occur in accordance with trial specific working instructions.

***Group holding rules*.** If a group holding rule is activated, further vaccinations won’t occur until it is deemed appropriate to restart, by the MHRA: if more than 30% of vaccinations are followed by the same Grade 3, solicited local AE or solicited systemic AE or unsolicited AE, beginning within 2 days after vaccination and persisting at Grade 3 for >48 hrs. Other events that trigger the rule include related death, life-threatening reaction, SUSAR, acute allergic reaction or anaphylactic shock. The study can also be put on hold upon advice of the Chief Investigator, Sponsor, MHRA, REC or DMEC.

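### Durability of the immune response is defined as stability from day 21 to end of season, which measures waning and cannot on its own show that an induced response persists

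*Protocol article*

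**What the plan says.** The immunogenicity paragraph of the Statistics section first names a between-group difference in the size of T-cell and antibody responses as the main sub-cohort analysis, without giving a time point. It then specifies "comparing the change in these immunological parameters from baseline to 21 days after vaccination between the groups". The next step has its own purpose, "To assess the durability of immune responses post-vaccination", and its own measure: "the stability of immunological parameters between the post vaccine time point and end of season time point will be assessed". Values are log10 transformed, and for the methods "we will use appropriate regression or correlation methods to carry out the analysis".

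Table 3 gives the sampling: "Blood samples drawn at enrolment (before vaccinations), day 21 and at the end of the influenza season". On size, the Sub-cohort section says "A sub-cohort of participants (50 for each of two seasons) will be recruited to assess the immunogenicity". On the arms, the Interventions section says "Participants are randomly assigned to either the control (licensed IIV and placebo) or intervention group (licensed IIV and MVA-NP+M1".

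**The concern.** A vaccine response is a departure from baseline, and a vaccine effect is a departure from control. A contrast that starts at day 21 refers to neither. It describes how far values move after day 21, which is waning. It does not say whether anything was induced, or whether MVA-NP+M1 recipients still exceed controls when the season ends.

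The Abstract rests the case for the vaccine on T-cell responses that may give long protection, so the excess over control at end of season is the durability question of interest. If stability is reported as the answer, an arm with little response can be described as durable, and an arm with a partly retained boost can be described as less so.

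A later analysis plan may say how stability is computed. The two time points that define it, which leave out baseline, are already fixed here.

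**Working it through.** **Inputs.** From the protocol: samples at enrolment (B), day 21 (P) and end of season (E); log10 scale; 5% two-sided tests; 50 participants in each of two seasons, so 100 in all and about 50 per arm at 1:1. The protocol gives no fold-rise, retained fraction or standard deviation (SD) for the assays, so those below are assumptions. It states no durability figure, so there is none to reproduce.

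**Step 1: what the contrast measures.** The stability contrast, read as a change, is log10(E/P). Persistence relative to baseline is log10(E/B). Where half the gain is kept, it is half of the arithmetic gain.

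| Scenario | log10(E/P) | log10(E/B) |
|---|---|---|
| No response | 0.000 | 0.000 |
| Twofold rise, all kept | log10(2/2) = 0.000 | log10(2) = +0.301 |
| 1.5-fold rise, half kept | log10(1.25/1.5) = -0.079 | +0.097 |
| Twofold rise, half kept | log10(1.5/2) = -0.125 | +0.176 |
| Threefold rise, half kept | log10(2/3) = -0.176 | +0.301 |
| Fourfold rise, half kept | log10(2.5/4) = -0.204 | +0.398 |
| Twofold rise, all lost | log10(1/2) = -0.301 | 0.000 |

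The first two rows are opposite findings with the same stability score. This needs no assumption about variance. Among the half-kept rows, a larger persisting response goes with a worse stability score.

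**Step 2: correlation instead of change.** Subtracting the same amount from every end-of-season log10 value leaves the correlation with day 21 unchanged. With an assumed between-person SD of 0.5 and within-person SD of 0.25, r = 0.25/(0.25 + 0.0625) = 0.80, whether the boost is kept or lost. In simulation with 50 per arm and a 0.3 log10 boost fully lost, the correlation was still significant in 100% of trials. With individual variation in the boost (mean gain 0.3 log10, 20% to 80% kept, assay SD 0.15), r was 0.79 to 0.80 in boosted arms against 0.80 with no response (between-person SD 0.3), and 0.89 to 0.91 against 0.92 (SD 0.5). Correlation therefore hardly penalises a boosted arm, but it does not measure persistence either.

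**Step 3: size, if the change were compared between arms.** The protocol does not state this comparison; it is shown only to size the possibility. For a twofold rise with half the arithmetic gain kept against a control with no response (difference 0.125), 50 per arm gives an 88%, 55% or 34% chance that the boosted arm is significantly less stable, at an SD of change of 0.2, 0.3 or 0.4. A control arm that rises 1.2-fold and keeps half still scores only log10(1.1/1.2) = -0.038.

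**Step 4: the alternative under the same conditions.** Take a 0.3 log10 boost with half kept on the log scale (0.15), no control response, and the SDs of step 2.

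- Change from day 21: SD = 0.25 × √2 = 0.354; standard error = 0.354 × √(2/50) = 0.071; 0.15/0.071 = 2.12, so the boosted arm is significantly less stable in about 56% of trials.
- End of season adjusted for baseline: residual SD = √[0.3125 × (1 - 0.80²)] = 0.335; standard error = 0.335 × √(2/50) = 0.067; 0.15/0.067 = 2.24, so the retained benefit is detected in about 61%.

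Simulation gave the same 56% and 61%. The adjusted comparison found vaccine above control in 99% of trials with the whole boost kept, and in 2% to 3% with no effect or full loss. For within-person SD from 0.15 to 0.35, the half-kept figures run from 93% to 33% (less stable) and from 94% to 36% (benefit detected). With 37 per arm, which applies the main trial's 25% attrition, they are 43% and 47%.

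**The case against.** The strongest reply is that the text should be read in sequence. It compares the rise to day 21 between arms and then asks what happens afterwards, so an arm with no rise would already be shown as such. The change after day 21 is a legitimate measure of waning. This stands as partial mitigation. However, the day-21 comparison shows whether an excess arose, not whether it is still there at end of season.

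Second, the opening aim of comparing response magnitude between groups is not limited to day 21, and the general text provides mixed models for continuous secondary outcomes. An end-of-season comparison would fit within that wording. This also stands: such a comparison is not excluded. It is just not set out, and the sentence that addresses durability points elsewhere.

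Third, a reader might infer that the plan would declare an ineffective vaccine durable, or would favour placebo over a working vaccine. The document does not support that. It defines no stability test, sets no between-arm comparison of stability, and does not say that more stable is better. Nor does it assign correlation to the durability question; the methods sentence covers all the immunogenicity analyses. Controls receive the licensed vaccine, and the readouts include "antibody responses (using influenza hemagglutination inhibition assay) between the two groups", so control antibody can be expected to rise and wane too. A control arm with no response is plausible mainly for T cells, and there only as an assumption.

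Finally, how stability is computed could be left to an analysis plan. That covers the formula, but not the choice of a contrast that omits baseline.

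**Conclusion.** The point holds in a limited form. As worded, the durability measure describes waning from day 21. On its own it cannot separate a fully kept response from no response, and a correlation between the two time points would not reveal uniform waning. That conclusion follows from algebra and needs no assumed values.

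Every percentage above is conditional on assumed variances, boosts and retained fractions, and on comparisons that the protocol does not prescribe. They show that the distortion could be material with about 50 per arm; they do not predict this trial's result.

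This is a secondary analysis in a sub-cohort of 100, so the primary endpoint and the sample size are unaffected. It is a cheap improvement to a stated analysis and does not threaten the trial's main conclusion.

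**What to change.** Reword the durability sentence in the protocol or analysis plan:

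- Define durability as the ratio of geometric means, MVA-NP+M1 over control, at the end-of-season sample, from a linear model on log10 values adjusted for the log10 baseline value, with a 95% confidence interval.
- Report the fold change from baseline to end of season in each arm.
- Keep the end-of-season to day-21 ratio as a description of waning only, presented next to the rise to day 21.
- State that neither a correlation between the two time points nor a non-significant change will count as evidence of durability.

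The cost is wording and a little more analysis, since all three blood samples are already planned. The downside is that a durability claim becomes harder to meet, because it requires the excess over control to persist.

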### Discontinuation/withdrawal

Participants may withdraw voluntarily, on the decision of the Investigator or on the advice of the DMEC. If a participant withdraws from the study, data and blood samples collected before their withdrawal will be used/stored unless they specifically requests otherwise.

### Monitoring

Regular monitoring at investigator sites is performed according to ICH GCP and a monitoring plan.

### Joint Data Monitoring and Ethics Committee and Trial Steering Committee

A joint DMEC and Trial Steering Committee periodically reviews and evaluates the accumulated study data for participant safety, study conduct and progress, and efficacy. The committee includes three appropriately qualified members. The DMEC will review SAEs deemed at least possibly related to study interventions.

### Interim analyses

Three interim safety reviews are planned to evaluate the safety data accumulated up to the following time points (by the DMEC):

1. After the first 100 participants have been randomised2. The end of vaccinations in the first year of the study3. The end of the 1
^st^ year of follow-up

## Discussion

There is an urgent and pressing demand for improved vaccination strategies against a broad spectrum of influenza virus strains. INVICTUS aims to investigate whether MVA-NP+M1 is capable of providing protection against a broad spectrum of influenza A virus strains with better immune responses in older people, who are at higher risk of severe influenza disease.

INVICTUS is the first clinical trial to investigate whether the combination of MVA-NP+M1 and the seasonal vaccine, reduces ILI symptoms in patients, which would be both clinically useful and considerable step forward in vaccine development. 

## Data availability

### Underlying data

No underlying data are associated with this article.

### Extended data

Open Science Framework. F1000Research INVICTUS Protocol Manuscript.
https://doi.org/10.17605/OSF.IO/T6P2B
^10^.

Extended data are available under the terms of the
Creative Commons Zero "No rights reserved" data waiver (CC0 1.0 Public domain dedication).

### Reporting checklists

SPIRIT checklist for “A phase IIb study to determine the safety and efficacy of candidate INfluenza Vaccine MVA-NP+M1 in combination with licensed InaCTivated inflUenza vaccine in adultS aged 65 years and above (INVICTUS): a study protocol”.
https://doi.org/10.17605/OSF.IO/T6P2B
^10^.
